### Participants

All consecutive patients of any ages with acute burns of indeterminate depth (assessed by the treating clinician), who are seen within 5 days post burn at one of the three burn centres, are eligible.

Inclusion criteria:

• Patients with acute burns of indeterminate depth (=intermediate depth; the burn wound is not obviously superficial or obviously full thickness)

• Outpatient treatment or admission in one of the three Dutch burn centres

• Presentation within 5 days post burn

Exclusion criteria:

• The presence of full thickness wounds, next to intermediate wounds

• Topical treatment/dressings that impair scanning (e.g. hydrocolloid dressings)

• Patients with peri-orbital facial burns, in which the eyes are unable to shield

• Patients or their next of kin if they are under aged or temporary incompetent who can not be expected to give informed consent e.g. because of cognitive dysfunction or poor Dutch proficiency.

• Patients with a TBSA burned > 20%

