##### Diagnostic decisions: diagnostic effect of LDI and accuracy

In the ‘new diagnostic strategy’ group the diagnostic effect of the introduction of LDI will be assessed on the scanning day by comparing diagnostic decisions of burn clinicians, just before and after the use of LDI.

Possible diagnostic decisions before LDI are:

• Superficial partial thickness burn (no study wound)

• Intermediate burn, the burn wound is not obviously superficial or full thickness (if parts of a burn wound are obviously full thickness, this will be recorded also)

• Deep partial thickness of full thickness burn (exclusion patient from study)

Possible diagnostic decisions after LDI are [12]:

• Superficial partial thickness burn, will heal within 14 days

• Intermediate partial thickness burn, will heal between 14–21 days (the spectrum of an ‘intermediate burn’ is smaller after the use of LDI compared to before the use of LDI)

• Deep partial thickness or full thickness burn, will not heal within 21 days

Accuracy of LDI in our study patients will be checked also. Results of laser Doppler imaging are compared with the reference tests: time of wound healing (from burn date until >95% reepithelialisation) and biopsies. In our study protocol, wounds with a healing potential ≤ 21 (assessed by the LDI) are considered as superficial or intermediate partial thickness and wounds with a healing potential > 21 days are considered as deep partial thickness or full thickness. Only in case of surgery a 3 mm-punch biopsy will be taken as a reference test to assess burn depth [1]: in a superficial burn the basal membrane is partially destroyed; in a deep partial thickness burn the basal membrane is entirely destroyed and the dermis partially destroyed; in a full thickness burn, the dermis is also completely destroyed.

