## Statistical analysis

Data will be primarily analysed according to the intention-to-treat principle. We assume that time to LDI will be equal in both diagnostic groups, as a result of randomisation. Thus, the differences in effects (e.g. time to wound healing) and costs will be assessed from randomisation onwards.

Differences in time to wound healing (numbers of days between LDI and day of > 95% reepithelialisation) and timing of surgery in both diagnostic strategy groups will be analysed with Kaplan-Meier curves and log rank test.

Quality of life (derived from the ItQol-47 and EuroQol-6D), scar quality (assessed by the Cutometer®, Dermaspectometer® and POSAS) and length of hospital stay will be analysed using the independent-sample-t-test (in case of normal distribution) or the Mann–Whitney test (non-normal distribution).

Differences in diagnostic and therapeutic decisions will be analysed with the Chi-square test. Diagnostic accuracy will be assessed by calculating sensitivity and specificity of the LDI compared to the reference test: time to wound healing (in conservative treated patients) or biopsy (in surgical treated patients). In addition, receiver operating characteristic (ROC) curves will be calculated for both diagnostic groups.

Differences in mean costs (after randomisation) will be analysed by the Mann–Whitney test, since healthcare costs are typically highly skewed. Non-parametric techniques (bootstrapping) will be used to derive a 95% confidence interval for the differences in distributions of the costs.

The cost-effectiveness analysis and cost-utility analysis are performed by dividing the differences in average costs by the differences in average effects or utility. In a sensitivity analysis, the impact on cost-effectiveness of statistical uncertainty on the main study outcomes will be determined (uni- and multivariable).

Data analysis will be performed using SPSS-software (Statistical Package for the Social Sciences).

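### The chi-square test for the diagnostic effect of LDI is applied to paired decisions whose before-LDI value is fixed by eligibility, so its p-value is uninterpretable

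*Protocol article*

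**What the plan says.** The Statistical analysis section covers two outcomes with one sentence: "Differences in diagnostic and therapeutic decisions will be analysed with the Chi-square test".

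The section on diagnostic decisions defines the diagnostic effect within the new-strategy group only. It is assessed on the scanning day by "comparing diagnostic decisions of burn clinicians, just before and after the use of LDI". Three decisions are listed as possible before LDI:

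- "Superficial partial thickness burn (no study wound");
- "Intermediate burn, the burn wound is not obviously superficial or full thickness";
- "Deep partial thickness of full thickness burn (exclusion patient from study").

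After LDI the three options are healing within 14 days, between 14 and 21 days, and not within 21 days. The section adds that the intermediate class covers a narrower range after the scan than before it. The Participants section includes "Patients with acute burns of indeterminate depth (=intermediate depth; the burn wound is not obviously superficial or obviously full thickness").

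For accuracy, the Statistical analysis section names as reference test "time to wound healing (in conservative treated patients) or biopsy (in surgical treated patients"), and plans ROC curves for both diagnostic groups. The Abstract says that the scan result is given to the treating clinician in the new-strategy group only.

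**The concern.** There are two faults, and the second is the deeper one.

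First, the before and after decisions concern the same patient. A chi-square test that compares the two distributions treats them as independent samples.

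Second, the decision before LDI cannot vary. A superficial wound is not a study wound and a deep one leads to exclusion, so every analysed wound is intermediate before the scan. The null hypothesis of no difference then says that no wound at all is reclassified, and a single reclassified wound disproves it. Because the intermediate class is also narrowed by definition after the scan, movement out of it is partly a change of scale.

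The effect on diagnostic decisions is a stated aim in the Abstract, and the Discussion presents the analysis of changes in diagnosis and therapy as a strength. A significant p-value here would probably be read as evidence that LDI improves diagnosis, which it could not show.

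**Working it through.** The article gives no figure for this comparison, so there is none to reproduce. The check builds the table that the text implies.

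**Inputs.** The total of 200 patients is from the Intervention section. Equal allocation is assumed, since no ratio is stated, so N = 100 in the new-strategy arm, with one decision per patient. With the 5% drop-out from the Sample size section, N = 95. The two-sided 5% level is the one stated for the primary outcome. The number reclassified, k, is not in the article and is varied.

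**Table.** Before LDI: N intermediate, 0 other. After LDI: N − k intermediate, k other.

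**Pearson chi-square.** For this table the statistic reduces to 2Nk / (2N − k), on 1 degree of freedom. With N = 100:

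| k | Statistic | p, uncorrected | p, continuity-corrected | p, exact McNemar |
|---|---|---|---|---|
| 3 | 600/197 = 3.05 | 0.081 | 0.245 | 0.250 |
| 4 | 800/196 = 4.08 | 0.043 | 0.130 | 0.125 |
| 5 | 1000/195 = 5.13 | 0.024 | 0.070 | 0.063 |
| 6 | 1200/194 = 6.19 | 0.013 | 0.038 | 0.031 |

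The uncorrected test is significant from four patients and the corrected test from six. N = 95 gives the same thresholds (for k = 4, 760/186 = 4.09, p = 0.043). With three categories the statistic has the same value on 2 degrees of freedom, and significance again needs six patients (6.19, p = 0.045).

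**McNemar.** With every before-LDI decision intermediate, one discordant cell is k and the other is always 0. The exact two-sided p-value is 2 × 0.5^k, for example 2/64 = 0.031 at k = 6. It only counts k, so respecting the pairing does not repair the comparison.

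**Probability of a significant result.** With k binomial (100, q), this is P(k ≥ 4) for the uncorrected test and P(k ≥ 6) for the corrected one:

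| Assumed rate q | Uncorrected | Corrected | No change at all, (1 − q)^100 |
|---|---|---|---|
| 3% | 0.35 | 0.08 | 4.8% |
| 5% | 0.74 | 0.38 | 0.6% |
| 10% | 0.99 | 0.94 | 0.003% |
| 20% | about 1 | about 1 | about 0 |

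**Noise check.** If clinicians simply adopted a scan that assigned the three classes at random, two thirds of wounds would be reclassified and the test would reject with probability about 1. The test cannot tell an informative scan from an uninformative one.

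**Between-arm reading.** The article defines no post-LDI diagnostic decision for the current-strategy arm. On the only scale defined for that arm, all its wounds are again intermediate, so the problem remains. Therapeutic decisions differ: they are compared on the day of randomisation and read naturally as a comparison of two independent groups, for which chi-square is appropriate.

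**The case against.** The strongest reply is that LDI is an add-on test for wounds that the clinician cannot classify, so the share it resolves into superficial or deep is a meaningful result. That stands: the outcome has descriptive value, and the fault lies in the significance test attached to it. It is also true that the outcome is secondary. The primary log-rank comparison, the sample size and the economic evaluation do not depend on it. A fuller protocol or analysis plan may word the method differently, but the article does name both the test and the categories, so this is not a matter of omitted detail.

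Several stronger readings might be inferred, and the article does not support them:

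- *A change is guaranteed.* It is not. If every post-LDI decision were 14 to 21 days, nothing would change. The decisions compared are also the clinician's, not the scan colours, and the Discussion expects clinicians to rely less on LDI at first.
- *Patients judged deep are excluded from one arm only.* The Abstract places clinical assessment and LDI in all patients before randomisation, and the Participants section applies eligibility to everyone.
- *The biopsy classes do not match the LDI classes.* Both collapse to the same two-way split, since LDI is cut at 21 days into superficial or intermediate versus deep partial or full thickness.
- *Specificity is inflated by a known amount in the new-strategy arm, and the arm with LDI hidden is clean.* A figure would need a biopsy error rate and a degree to which surgery follows LDI, and the article gives neither. The hidden arm has its own risk. Non-deep wounds operated on clinical grounds and misread as deep by biopsy would mostly be LDI-negative and would lower apparent sensitivity.

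One part of the accuracy point remains. In the new-strategy arm, the disclosed LDI result can influence who has surgery, and so which reference test is applied.

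**Conclusion.** The chi-square test is wrong as written for the diagnostic effect of LDI. The pairing and the fixed before-LDI value follow from the text without any assumption. The size rests on about 100 patients in the new-strategy arm and one decision per patient: significance from four reclassified patients uncorrected, or six with correction, and near certainty once about 10% or more are reclassified. The article gives no expected rate. At 3% to 5% the result would not be near certain (0.35 to 0.74 uncorrected). Rates that low look unlikely, as the Background puts clinical accuracy at about two thirds, although that is not the same quantity.

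The point should be corrected, but it concerns a secondary outcome and does not threaten the trial's main conclusion.

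**What to change.** 1. Remove the chi-square test for the before/after diagnostic comparison. Report the proportion of intermediate wounds reclassified as superficial or deep after LDI, with a 95% confidence interval. At N = 100 the half-width is at most about 1.96 × √(0.25/100) = 0.098, or 10 percentage points. If several wounds per patient are counted, the interval should allow for clustering.
2. For patients still to be enrolled, have the clinician record the expected healing class on the LDI scale (<14, 14–21, >21 days) before the LDI result is seen and before the envelope is opened. In the new-strategy arm, cross-tabulate it with the post-LDI class and use a paired test: Stuart-Maxwell or Bowker, or McNemar at 21 days. Such a test shows whether decisions shift. Whether the shifts are correct is a matter for the accuracy analysis.
3. State that chi-square applies to the between-arm comparison of therapeutic decisions.
4. Report sensitivity and specificity separately by arm, as is already planned for the ROC curves, and do not describe either arm as free of bias.

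The cost is one item on the scan-day form plus analysis wording. Inclusion began in December 2011, so patients already enrolled contribute only to the reclassified proportion. Accuracy estimates by arm are less precise than pooled ones.

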Data registration will start on the day of randomisation. Data regarding patients’ baseline characteristics and health-care use will be obtained from patient records and the electronic hospital administration.

*Other healthcare costs and non healthcare costs* will be calculated based on charges as a proxy of real costs [24] with the help of data obtained from patient questionnaires after 3 months. Other healthcare costs include nursing-home and rehabilitation centre, homecare, visits to general physicians and allied health professional outside the hospital. Indirect non-healthcare costs include productivity loss in patients and partners or parents (if applicable), and direct non-healthcare costs include patient travel costs.

To measure the economic impact of LDI in burn care cost-effectiveness will be assessed by calculating the incremental cost-effectiveness ratio, defined here as the costs for the ‘new diagnostic strategy’ (minus savings) divided by the difference in wound healing time (measured from randomisation) between the ‘new diagnostic strategy’ and ‘current diagnostic strategy’. Secondary, a cost-utility analysis will be performed, i.e., as cost per Quality Adjusted Life Years (QALY). The cost-utility ratio can be calculated in patients ≥ 5 years only. In children under the age of 5 years, the EuroQol-5D is not validated and no questionnaires are available that allow the calculation of utility scores [18,19]. Overall utility scores for population-based quality of life (derived from the EuroQol-5D) will be obtained and expressed as QALY’s. QALY’s will be calculated by multiplying the utility of a health state by the time spent in this health state using the Dutch valuation tariff [26]. Policymakers and health economists have proposed that costs varying from €25,000 up to €75,000 per QALY may be considered as acceptable [27]. In accordance with guidelines for differential discounting, effects will be discounted at a rate of 1.5% and costs at 4% per year [24].

In case no differences will be found in wound healing and quality of life, the economic evaluation will be based on a cost-minimisation analysis, that consists of a comparison of total costs in both diagnostic strategies.

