### Sample size

A total of 57.5% of admitted burn patients in the Netherlands is treated conservatively (unpublished data, Dutch Burn Repository R3, 2011). The time to wound healing in patients without surgery is approximately 13 days, this will not change after the introduction of LDI. In the 42.5% of surgically treated patients we do expect an effect on wound healing time, because of an earlier operation. The mean time to first transplantation is 14.0 days post burn, the mean time to wound healing is 5 days after surgery [28], resulting in a mean time to wound healing of 19.0 days. The overall mean time to wound healing for all patients combined is 15.6 days ((57.5%*13+ 42.5%*19)/100).

Petrie et al. describe a reduction of 5.3 days in LOS in patients undergoing surgery, after the introduction of the LDI. As a result, in our population, an overall effect of 2.25 (57.5%* 5.3) days can be expected, with a standard deviation of 5 days. A 2-sided test with an α level of 0.05 and a β level of 0.20 (power 0.80) indicates a required total sample size of 190 patients. We expect a low drop out rate because of a short time to follow up to assess primary outcome (time to wound healing). With a 5% drop out we need a total sample size of 200.

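### The cost test (Mann-Whitney) does not test the mean cost difference that it is assigned to and that the cost-effectiveness ratios use; the bootstrap interval is not tied to that difference either

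*Protocol article*

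**What the plan says.** Three consecutive statements in the Statistical analysis section of the protocol article bear on this.

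- The test: "Differences in mean costs (after randomisation) will be analysed by the Mann–Whitney test, since healthcare costs are typically highly skewed".
- The interval: "Non-parametric techniques (bootstrapping) will be used to derive a 95% confidence interval for the differences in distributions of the costs".
- The ratios: "The cost-effectiveness analysis and cost-utility analysis are performed by dividing the differences in average costs by the differences in average effects or utility".

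The section on the economic evaluation adds a fallback if neither wound healing nor quality of life differs: "the economic evaluation will be based on a cost-minimisation analysis, that consists of a comparison of total costs in both diagnostic strategies".

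The article does not give the Mann-Whitney test a merely descriptive role or assume equal distribution shapes. It does not say that the bootstrap interval is for the mean difference, or which result governs if test and interval disagree.

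**The concern.** The plan names a quantity, the difference in mean costs, and then a test of something else. The Mann-Whitney test asks whether a patient in one arm tends to cost more than a patient in the other. That matches a comparison of means only under restrictive conditions, such as a pure shift between distributions of the same shape. Skewed costs are a reason to be careful about how uncertainty in the mean is estimated. They are not a reason to leave the mean, because total spending and both ratios are built on it.

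Equal shapes are doubtful by the trial's own reasoning. The Sample size section expects no change in healing time in conservatively treated patients and places the effect in the operated ones: "In the 42.5% of surgically treated patients we do expect an effect on wound healing time, because of an earlier operation". The economic section counts the LDI scan as an intervention cost. If that cost is charged to every patient in the new-strategy arm, a small increase for all is combined with a larger saving in an expensive minority. Ranks and means can separate in that pattern.

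At stake is how the cost result is reported. A real mean saving could appear beside a non-significant p-value, or the ranks could lean the other way. In the cost-minimisation fallback the cost comparison carries the whole economic conclusion, and the only named cost test does not address mean total cost.

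**Working it through.** **No figure to reproduce.** The article gives no cost mean, spread or scan price. The mismatch follows from the text alone: the test targets rank ordering, while the ratios come from "dividing the differences in average costs by the differences in average effects or utility". The calculations below only illustrate its possible size.

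**Inputs from the article.**
- Total sample size: "A 2-sided test with an α level of 0.05 and a β level of 0.20 (power 0.80) indicates a required total sample size of 190". The allowance for drop-out is stated separately: "With a 5% drop out we need a total sample size of 200". Equal allocation is assumed, giving 190 / 2 = 95 per arm after drop-out, or 200 / 2 = 100 per arm.
- Operated share 42.5%, conservative share 57.5%.
- Two-sided 5% level, which the article states for the primary outcome and which is borrowed here.

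**Assumptions.** All cost levels and spreads are assumed. In sets A and B, costs are log-normal within the conservative and operated groups with log-SD 0.6, so a group mean is its median times exp(0.6²/2) = exp(0.18) = 1.197. EUR 600 is added to every new-strategy patient for the scan. Scans are done in both arms, so this assumes the cost is charged to the new strategy only. The comparator is a Welch t-test on means.

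**A. Small saving.** The operated group's median falls by EUR 2,500.
- True mean difference = 600 − 0.425 × 2,500 × 1.197 = 600 − 1,272 = −EUR 672.
- Conservative/operated medians were varied from 3,000/8,000 to 8,000/20,000, with 95 per arm.
- Mann-Whitney rejects in about 5% of trials and Welch in about 6% to 16%.
- Mann-Whitney is significant against the direction of the observed mean difference in at most about 0.3% of trials.

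**B. Larger saving.** Conservative median 4,000; operated median falls from 20,000 to 12,000.
- True mean difference = 600 − 0.425 × 8,000 × 1.197 = 600 − 4,070 = about −EUR 3,470.
- With 95 per arm, Mann-Whitney rejects in about 9% of trials and Welch in about 55%.

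In B the scan cost moves the 57.5% conservative patients up in rank. The saving moves operated patients down, but most of them still rank above the conservative group. The ranks largely cancel; the means do not.

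**C. Range of behaviour under other assumed shapes, 100 per arm.**

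| Assumed scenario | Mann-Whitney rejects | Welch rejects |
|---|---|---|
| Identical log-normal, log-SD 1.0 | 5.3% | 4.9% |
| Equal means, log-SD 1.0 vs 0.8 | 28% | 5.2% |
| Equal means, log-SD 1.2 vs 0.8 | 77% | 6.6% |
| Equal medians, one mean 49% higher | 4.8% | 46% |
| Mixture, scan adds 500, true means equal | 14% | 4.7% |

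When the distributions are identical, both tests hold their level. When shapes differ, Mann-Whitney can reject often although the means are equal, or seldom although they differ widely.

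**The case against.** The strongest reply is that the decision quantity is already on the right scale. Both ratios use average costs, no adoption rule depends on the Mann-Whitney p-value, and the fallback is triggered by the healing and quality-of-life results, not by the cost test. A sensitivity analysis of statistical uncertainty in cost-effectiveness is also planned. All of this stands, and it limits the severity. A reader might infer that the ratio itself, or its point estimate, will be wrong. The article does not support that: neither changes with the choice of test.

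A second reply is that the bootstrap sentence directly follows one on mean costs, so an interval for the mean difference is a natural reading. That reading is possible, and a reader who infers that the bootstrap certainly targets something else goes too far. But a difference in distributions is not a single parameter. If the mean is intended, the report would still carry an interval for one quantity beside a p-value for another.

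A third reply is that the numbers are invented. It stands in part. A reader might infer from set A that the rank test hides a real saving, but a test of means would also usually miss EUR 672 at this sample size. The low rejection rate there mainly reflects a small saving against a wide spread. Set B and the table show that divergence can be large, not that it will be large in this trial.

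That the article is condensed does not remove the point, because the test and its target are stated outright.

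**Conclusion.** The point holds as a mismatch between the named test and the stated quantity, and this rests on no simulation. The Mann-Whitney p-value does not belong to the mean cost difference, and the bootstrap interval as worded is not fixed to it. The cost p-value can therefore disagree with the numerator of the ratio.

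The size cannot be known from the article. With the assumed mixtures it runs from almost nothing, when the saving is too small for either test, to a rejection rate of about 9% against about 55% when the saving is about EUR 3,470. These figures rest on log-normal costs, log-SD 0.6, a EUR 600 scan cost charged to the new-strategy arm only, and 95 patients per arm.

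It should be fixed, but it is not a critical fault. It affects a secondary economic comparison. The primary outcome, sample size and randomisation are untouched, and the cost point estimate and the ratios are already defined on means.

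**What to change.** Replace the two cost sentences in the Statistical analysis section with one statement: the cost comparison is the difference in arithmetic mean total cost between the arms, and the bootstrap 95% confidence interval is for that mean difference. Drop the Mann-Whitney test for costs, or keep it labelled as descriptive and state that it does not decide the cost conclusion. Apply the same statement to the cost-minimisation fallback.

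This costs a change of wording. The bootstrap is already planned, and no new data or design change is needed. The change should be made and dated before the cost data are analysed, so that the choice between test and interval is not made after seeing the results.
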